#### 2.3.2 Secondary outcomes

Items 1–4 below will be compared between baseline (month 0) and each time point in the pre-observation, observation, and follow-up periods, and between 6 months after imeglimin administration and each time point in the follow-up period. The change from baseline (maximum and mean values) in the pre-observation and observation periods will also be evaluated.1. Erythrocyte lifespan

Erythrocyte lifespan is calculated by measuring the carbon monoxide (CO) concentration in exhaled breath using a Carbolizer (Taiyo Co., Ltd., Osaka, Japan) and using the Strocchi et al., formula shown below (Strocchi et al., 1992):

Erythrocyte lifespan (days) = K × hemoglobin (g/mL)/endogenous CO (ppm).

K = 1380 (conversion factor).2. Erythrocyte deformability

Erythrocyte deformability is measured using a blood fluidity measuring device MC-FAN (Optima Inc., Tokyo, Japan). The microchannel array passage time of 100 μL heparinized whole blood is an index for blood fluidity.3. Red blood cell count, white blood cell count, hemoglobin concentration, and hematocrit (Ht)4. Corpuscular constant (mean corpuscular volume: MCV, mean corpuscular hemoglobin concentration: MCHC, mean corpuscular hemoglobin content: MCH)

Items 5 and 6 below will be compared between baseline and the pre-observation or observation periods.5. Measured values of HbA1c, GA, and 1,5-AG, change from baseline, and percent reduction in blood glucose with baseline as 100% (percent reduction in blood glucose will also be compared between each index at each time point)6. GA/HbA1c and 1,5-AG/HbA1c ratios

For items 7 and 8 below, data measured by the FGM system using FreeStyle Libre Pro (Abbott Diabetes Care Inc., Alameda, CA, United States of America) will be used to compare baseline with each time point during the observation period (up to 3 months after imeglimin administration). FreeStyle Libre Pro should be used following the package insert.7. Change in mean daily glucose levels and percentage decrease in blood glucose (baseline is the day before imeglimin administration)8. Mean 14-day glucose levels, estimated HbA1c levels, glucose management indicator (GMI), and respective percentage decreases in glycemia (baseline is 14 days before imeglimin administration):

Estimated HbA1c (%) = (mean glucose [mmol/L] + 2.59)/1.59.

GMI (%) = 3.31 + 0.02392 × (mean glucose [mg/dL])9. Comparison of measured HbA1c levels and estimated HbA1c values at each time point in the pre- and post-observation periods and the respective percentage reduction in blood glucose at each time point

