## 2 Methods/design

### 2.1 Design

The INFINITY study (Comparative evaluation of clinical glycemic control markers treated with ImeglimiN and its eFfect on erythrocytes IN patIents with TYpe 2 diabetes mellitus) is a single-center, single-arm, open-label, prospective study. In clinical practice, the hypoglycemic effect of imeglimin in patients with T2D may differ when measured by HbA1c and GA levels. This study will be conducted in a single-arm, exploratory study (Table 1) because the prolonging of erythrocyte lifespan is postulated as the cause of this divergence. This study will compare HbA1c with the rate of glycemic reduction over time for GA or 1.5-AG to assess whether HbA1c is an appropriate measure. Continuous blood glucose variability measured using flash glucose monitoring (FGM) will also be examined related to changes in these indices to ensure reliability. In addition, because the effect of imeglimin on erythrocyte lifespan is a possible cause of HbA1c deviation, hemoglobin concentration, erythrocyte lifespan, and erythrocyte deformability will also be examined as effects on erythrocytes. Furthermore, if imeglimin ameliorates erythrocyte deformability, it is expected to have the potential to improve peripheral arterial occlusive disease, so an index of arteriosclerosis will also be measured.

**TABLE 1 T1:** Overview of visits and tests schedule.

Item	At informed consent	Pre-observation (months)		Observation period (months)							Follow-up period (months)			At discontinuation		
		−2	−1	0	1	2	3	4	5	6	7	8	9	
Allowable ranges of visits (±weeks)		±2	±2	±2	±2	±2	±2	±2	±2	±2	±2	±2	±2			
Informed consent	X															
Demography	X															
Study drug adherence					X	X	X	X	X	X				X		
Height, body weight				X	X	X	X	X	X	X	X	X	X	X		
Blood pressure, pulse rate				X	X	X	X	X	X	X	X	X	X	X		
Blood tests		X	X	X	X	X	X	X	X	X	X	X	X	X		
Urinalysis				X	X	X	X	X	X	X	X	X	X	X		
Erythrocyte lifespan		X	X	X	X	X	X	X	X	X	X	X	X	X		
Erythrocyte deformability			X	X	X	X	X	X	X	X	X	X	X	X		
Arteriosclerosis/inflammation test				X						X			X	X		
FGM test		X	X	X	X	X	X									
Adverse events		X	X	X	X	X	X	X	X	X	X	X	X	X		

Abbreviations: FGM, flash glucose monitoring.

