The observation period will be 6 months as the shortest period to confirm the divergence in the rate of glycemic reduction. The decrease in HbA1c after imeglimin administration is reportedly gradual, reaching a maximum approximately 6 months after the start of administration (Dubourg et al., 2021; Dubourg et al., 2022; Reilhac et al., 2022). In addition, a 2-month pre-treatment observation period will be set to evaluate various conditions before imeglimin administration, and a 3-month follow-up period after administration will be evaluated whether the effects of imeglimin on erythrocytes are reversible. A follow-up period of 3 months will be set to evaluate safety.

The study drug imeglimin (1,000 mg as TWYMEEG ^®^ tablets) will be administered orally twice daily, starting within 1 week after the end of the baseline examination and continuing through the observation period of 6 months. After 6 months, imeglimin will be discontinued, and the patients will be followed for 3 months. The use and dose escalation of an α-glucosidase inhibitor (α-GI) and metformin are allowed for glycemic control during the follow-up period.

The addition of all types of diabetes medications and the escalation of doses of α-GI and metformin taken during the 6-month observation period from the start of imeglimin administration (except in the case of discontinuation) are prohibited because of the possibility that these will affect the evaluation of this study. The use of antiplatelet and antithrombotic drugs is prohibited during the observation and follow-up periods.

The α-GI (excluding acarbose) and metformin used before the day of the consent will be continued in principle without dose change from the day of consent until the end of the 6-month observation period. Drugs deemed medically necessary can be added except for diabetes medications, antiplatelet agents, and antithrombotic agents.

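### Daily flash-glucose change is measured from a single pre-dose day, although the 14 pre-dose days that item 8 already requires would give a less noisy baseline for most later days

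*Protocol article*

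**What the plan says.** Section 2.3.2 lists two secondary outcomes from the same flash glucose monitor. Item 7 is "Change in mean daily glucose levels and percentage decrease in blood glucose (baseline is the day before imeglimin administration": one calendar day is the reference. Item 8 covers 14-day mean glucose, estimated HbA1c and the glucose management indicator, and its reference period is given as "baseline is 14 days before imeglimin administration". Both items are to "compare baseline with each time point during the observation period (up to 3 months after imeglimin administration". The article gives no reason for the different baselines. Section 2.8 assigns metric secondary outcomes a one-sample t-test or a signed rank test at each observation point. Section 2.1 and the Discussion say that the glucose monitoring is there to support the reliability of the comparison between HbA1c and the other glycemic markers.

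**The concern.** A single day's mean glucose varies with meals, activity and sensor error. When it is the only reference, that day's departure from the patient's usual level is subtracted from every later daily value. Looking at more follow-up days does not average it out: an unusual pre-dose day moves the patient's whole daily curve up or down. The same day is the divisor of every percentage decrease. The plan already calls for 13 further pre-dose days from the same device, so the extra noise is avoidable without collecting anything new. What is at stake is the precision of the daily curve, one of the trial's views of how quickly glucose falls.

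**Working it through.** **Inputs from the article.** One-day baseline (item 7); 14-day baseline (item 8); target of 30 patients (section 2.6). The article gives no variance for monitored glucose, so there is no plan figure to reproduce on this point. Its only precision calculation, for hemoglobin, does reproduce: a change of 0.7 with SD 1.0 g/dL, two-sided 0.05 and 90% power needs 24 patients (power 90.7%; 23 give 89.4%). It does not depend on item 7.

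**Assumptions.** Within-patient daily SD s = 15 mg/dL (range 10 to 25). Day-to-day correlation rho from 0 to 0.7, first-order autoregressive. SD of true change between patients t, with t/s from 0 to 2.

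**Step 1: a day well after the baseline.** The variance of a daily change is t² + s²(1 + v). With a one-day baseline v = 1. With a 14-day mean v = 1/14 = 0.071 for independent days, and 0.126, 0.194 and 0.326 for rho = 0.3, 0.5 and 0.7.

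| rho | t/s | One day (units of s²) | 14 days | Variance removed | SE ratio |
|---|---|---|---|---|---|
| 0 | 0 | 2.00 | 1.071 | 46% | 1.37 |
| 0.3 | 0 | 2.00 | 1.126 | 44% | 1.33 |
| 0.5 | 0 | 2.00 | 1.194 | 40% | 1.29 |
| 0.7 | 0 | 2.00 | 1.326 | 34% | 1.23 |
| 0 | 2 | 6.00 | 5.071 | 15% | 1.09 |
| 0.7 | 2 | 6.00 | 5.326 | 11% | 1.06 |

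**Step 2: in mg/dL.** For s = 15, n = 30, rho = 0 and t = 0, the standard error is 15 × √(2/30) = 3.9 with one day and 15 × √(1.071/30) = 2.8 with 14 days. The 95% half-width goes from 7.9 to 5.8 mg/dL. For s from 10 to 25 it goes from 5.3-13.2 to 3.9-9.7 mg/dL.

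**Step 3: the shared error.** With independent days and t = 0, two daily changes in the same patient correlate at 1/2 = 0.50 with the one-day baseline, and at 0.071/1.071 = 0.07 with the 14-day mean.

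**Step 4: the first days on drug.** Here the correlation between the baseline day and the treated day matters. For a day k days after the baseline day and t = 0, the one-day variance is 2(1 − rho^k). The 14-day variance is 1 + v − 2c, where c is the average of rho^(k+j) over j = 0 to 13.

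| rho | k | One day | 14 days | Change in variance |
|---|---|---|---|---|
| 0.3 | 1 | 1.40 | 1.07 | −24% |
| 0.5 | 1 | 1.00 | 1.05 | +5% |
| 0.5 | 2 | 1.50 | 1.12 | −25% |
| 0.7 | 1 | 0.60 | 0.99 | +66% |
| 0.7 | 2 | 1.02 | 1.09 | +7% |
| 0.7 | 3 | 1.31 | 1.16 | −11% |

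So at rho = 0.5 the one-day baseline is as good or slightly better on the first day. At rho = 0.7 it is better on the first two.

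**Step 5: the percentage decrease.** A noisy divisor understates the mean percentage decrease by roughly the squared coefficient of variation of the baseline. For an assumed mean of 160 mg/dL and s of 10 to 25, that is (10/160)² to (25/160)², about 0.4 to 2.4 percentage points. It is one fourteenth of that with 14 independent days. The mean absolute change has no such bias.

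**The case against.** The best defense is that a daily series starting from the day before dosing is a natural picture of onset, and that item 8 supplies the stable counterpart. Step 4 gives this some support: if adjacent days are strongly correlated, the day before dosing is as good a reference as 14 days, or a better one, for the first day or two. Wide differences in true response between patients also shrink the gain, to 11% at the low end examined. Both points stand, and they are why the one-day comparison should be kept in a supplementary role. They do not justify it as the only reference for a daily series that runs to month 3.

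A reader might go further and infer that the timing rules conflict. Section 2.1 has dosing "starting within 1 week after the end of the baseline examination", so the day before dosing might seem to lack sensor data, or on-drug days might seem to enter the 14-day baseline. The article does not support this. Both baselines are defined as before the first dose, so on-drug days are excluded by definition. A single wear that ends just before the first dose satisfies both items within the permitted week. When sensors are applied and removed is operational detail that a condensed article may leave to the full protocol; it refers device use to the package insert.

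**Conclusion.** The point holds as a modest loss of precision in one secondary outcome of an exploratory study. For days well after the baseline, the 14-day pre-dose mean removes about 11% to 46% of the variance of a daily change. This rests on assumed values of rho from 0 to 0.7 and t/s from 0 to 2, since the article reports no glucose variance. The figure of 3.9 against 2.8 mg/dL belongs to the favorable end of that range (independent days, no differences in true response).

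Three larger readings are tempting and should not be drawn. First, it is not true that every daily estimate gets noisier: the first day or two may not. Second, for the average change over 14 days the variance reduction would be 87% with independent days, but 14-day means belong to item 8, which already has a 14-day baseline. Third, the baseline-error component alone falls from 15/√30 = 2.7 to 15/√420 = 0.7 mg/dL, but that is not the standard error of a daily change.

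The error is random and leaves the mean absolute change unbiased; the effect on the mean percentage decrease is small. Item 8, the comparison of measured with estimated HbA1c in item 9, the primary hemoglobin endpoint and the sample size do not depend on the one-day baseline.

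**What to change.** For item 7, define the main baseline as the mean of all valid sensor days in the 14 days before the first dose, the same period as item 8, counting no day on or after the first dose. Use it for both the absolute change and the percentage decrease. Keep the change from the day before dosing as a supplementary description of onset over the first days. Record the change in the detailed analysis plan that section 2.8 says will be confirmed before database lock, and align the wording of item 7.

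The cost is a little more analysis work and a main daily curve that is a less literal picture of onset. It needs no visit, procedure or sensor beyond those that item 8 already implies.

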### 2.8 Statistical analysis

Summary statistics of the background data of the study participants will be calculated. For nominal variables, the numbers in each category and their percentages will be shown; for continuous variables, the numbers, mean, standard deviation, minimum, median, and maximum values will be calculated.

Two analysis groups will be used to assess the efficacy of this study: the full analysis set (FAS) and the per-protocol set (PPS), with FAS being the primary analysis. The FAS will be the population of eligible patients who received at least one dose of the study drug and have hemoglobin concentration measurements at baseline and at least one time point during the observation period. The PPS will be the population from the FAS, excluding those who deviated from the study protocol (e.g., use of prohibited concomitant drugs or study drug adherence of <80%). The safety analysis set (SAS) will be used to determine the safety of the study, and the SAS will be the population of patients who received at least one dose of the study drug and have data on any of the safety outcomes.

Summary statistics of hemoglobin levels before and at 6 months after imeglimin, the primary efficacy endpoint, will be calculated. A one-sample *t*-test or Wilcoxon’s signed rank test will be used to evaluate its statistical significance. For the secondary outcomes obtained from the metric data, summary statistics will be calculated for each observation point, a one-sample *t*-test or Wilcoxon’s signed rank test will be performed to evaluate statistical significance, and, if necessary, analysis of covariance, and multivariate analysis will be performed. If the data are non-normally distributed, appropriate data transformations will be applied. When statistical tests are conducted, the significance level will be set at 0.05 (two-sided), with the confidence coefficient for statistical estimation being 95% (two-sided).

In addition, the principal investigator and a biostatistician will confirm the detailed statistical analysis plan before the database is locked. All laboratory data are analyzed by an independent a biostatistician at the implemented in compliance with an outsourcing agreement.

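### Item 9 checks measured HbA1c against only one of the protocol's two glucose conversions, and the one chosen is 46% steeper than GMI, so a divergence seen there may depend on the equation.

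*Protocol article*

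**What the plan says.** All of this is in the protocol article.

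- **Section 2.3.2, item 8** lists "Mean 14-day glucose levels, estimated HbA1c levels, glucose management indicator (GMI), and respective percentage decreases in glycemia". Two conversions of the same mean glucose follow: "Estimated HbA1c (%) = (mean glucose [mmol/L] + 2.59)/1.59" and "GMI (%) = 3.31 + 0.02392 × (mean glucose [mg/dL" (the quote stops just before the closing brackets). Estimated HbA1c and GMI are listed as separate quantities.
- **Section 2.3.2, item 9** plans a "Comparison of measured HbA1c levels and estimated HbA1c values at each time point in the pre- and post-observation periods" together with "the respective percentage reduction in blood glucose at each time point". GMI is not named.
- **Section 2.3.2, text introducing items 7 and 8:** FGM data are used to "compare baseline with each time point during the observation period (up to 3 months after imeglimin administration"), so FGM on drug ends at month 3.
- **Section 2.8:** for secondary outcomes on a metric scale, "a one-sample *t*-test or Wilcoxon’s signed rank test will be performed to evaluate statistical significance". Covariance and multivariate analysis are allowed if needed, and a detailed analysis plan is to be confirmed before database lock.
- **Section 2.1 and the Discussion** give FGM a supporting role: it is meant to add reliability to the judgement on whether HbA1c is an appropriate measure on imeglimin.

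**The concern.** The study asks whether HbA1c reads high for a given glucose on imeglimin. Item 9 can answer that only if the conversion from glucose to the HbA1c scale has the right slope for these patients and this sensor. The protocol prints two conversions with clearly different slopes and uses the steeper one alone. When glucose falls, the steeper line predicts the larger drop. If true HbA1c tracks the shallower line, measured HbA1c falls short of the prediction although nothing has happened to the red cells.

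The error would run in the direction of the study's hypothesis, and a single-arm study has no control group to expose it. The pre-observation visits can show a constant offset between measured and estimated HbA1c. They cannot show a slope error while glucose is stable.

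**Working it through.** **Inputs from the document:** the two equations in item 8; entry HbA1c above 6.5% and up to 8.5% (section 2.2.1); 24 patients required and 30 targeted (section 2.6). The plan states no slope ratio, so it has no figure of its own to reproduce here.

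**Assumed, not in the document:** 18.016 mg/dL per mmol/L; the size of the glucose fall; all SDs in step 4.

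**1. Slopes on one unit**
- Estimated HbA1c: 1/(1.59 × 18.016) = 0.0349 % per mg/dL.
- GMI: 0.0239 % per mg/dL (0.02392 as printed).
- Ratio: 0.03491/0.02392 = 1.46. Unit factors from 18.0 to 18.018 give 1.459 to 1.461.

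**2. Where the lines cross**

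Setting (g/18.016 + 2.59)/1.59 = 3.31 + 0.02392g gives g of about 153 mg/dL, where both equations give about 6.97%. That is inside the entry range. The two nearly agree there and separate as glucose moves away.

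**3. Size of the discrepancy from 160 mg/dL**

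| Mean glucose (mg/dL) | Estimated HbA1c (%) | Reduction | GMI (%) | Reduction |
|---|---|---|---|---|
| 160 | 7.21 | – | 7.14 | – |
| 136 (15% fall) | 6.38 | 11.6% | 6.56 | 8.0% |
| 128 (20% fall) | 6.10 | 15.5% | 6.37 | 10.7% |

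The two differ by 3.6 and 4.8 percentage points of reduction. In HbA1c units, the 24 mg/dL fall gives 24 × 0.03491 = 0.84 against 24 × 0.02392 = 0.57, a gap of about 0.26 points.

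**4. How often this would reach significance**

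Simulation with 4000 replicates of the one-sample t-test (two-sided 0.05) on the difference in percentage reduction, counting only results in which measured HbA1c falls less than estimated HbA1c (nominal 2.5%). Assumed: baseline glucose 165 (SD 20) mg/dL, SD of the fall 10 percentage points, patient HbA1c offset SD 0.4, HbA1c noise SD 0.15, sensor noise SD 5 mg/dL. The noisier case uses 0.25 and 10. There is no lag and no erythrocyte effect. Ranges run from n = 24 to n = 30.

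| Truth | 10% fall | 15% fall |
|---|---|---|
| HbA1c follows GMI | 59% to 69% | 92% to 96% |
| HbA1c follows GMI, noisier | 24% to 29% | 48% to 59% |
| HbA1c follows estimated HbA1c | about 2% to 3% | about 2% to 3% |

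**5. Whether stricter rules would cure it**

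Same base-case inputs, testing the change in the gap (measured minus estimated) from the pre-treatment mean:
- Estimated HbA1c alone, GMI slope true, no lag: 75% to 99% false positives across falls of 10% to 15%. The change in gap does not remove the slope error.
- Significance required under both equations, estimated-HbA1c slope true, real elevation of 0.2 points: detected in only 0.1% to 5%, against 94% to 98% with that equation alone. The 0.26-point gap in step 3 cancels it.
- The same both-equations rule, GMI slope true, 70% of the HbA1c fall complete, no erythrocyte effect: false claims in 59% to 96%. Lag passes straight through.

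**The case against.** The strongest case against has four parts.

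- **The harm is conditional.** Two conversions that disagree do not show that the chosen one is wrong, and the rates above rest on assumed glucose falls and SDs. This stands. A reader might infer that item 9 will produce a false divergence; the document does not show which slope fits, so only the dependence on the equation is established.
- **Item 9 is not the deciding comparison.** The abstract and the Discussion rest the conclusion on divergence between HbA1c and GA or 1,5-AG together with erythrocyte lifespan. Those outcomes (items 1, 5 and 6) use neither equation. This stands too. It would be wrong to infer that the main HbA1c conclusion or the primary hemoglobin outcome is compromised.
- **The exact test may be left to the analysis plan.** Section 2.8 is generic, so it cannot be said that the protocol fixes a null under which the equation is exact. That is fair. The choice of comparator, however, is made in item 9 itself. Items 5 and 8 would supply the percentage reductions in HbA1c and GMI, so a reader could set them side by side, but item 9 does not plan that comparison.
- **Lag may matter more.** The introduction says HbA1c reflects 6 to 12 weeks and describes a transient divergence when glucose improves quickly, and FGM on drug stops at month 3. This is correct and is a separate limit. A slope mismatch shrinks the apparent fall and does not delay it, but item 9 compares percentage reductions, so it would still appear as divergence.

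**Conclusion.** The concern holds as a limited point about a supporting secondary analysis. Item 9 relies on one conversion whose slope is 46% steeper than that of the other conversion the protocol computes from the same glucose. For assumed falls of 15% to 20% from 160 mg/dL, the choice alone moves the expected reduction by 3.6 to 4.8 percentage points. Whether that becomes a false finding depends on which slope describes these patients. On the assumed inputs, the chance of a false result is 24% to 96% if HbA1c follows GMI, and nominal if it follows the estimated-HbA1c equation. The slope ratio follows from the printed equations and a standard unit conversion; the rates are illustrations. A change is worth making because the possible error favours the study's hypothesis and the remedy uses quantities already planned.

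**What to change.** In item 9, run the same level and percentage-reduction comparisons of measured HbA1c against GMI as well as against estimated HbA1c, and report both. Describe a divergence seen under only one equation as equation-dependent: it is not evidence that HbA1c reads high on imeglimin, and equally it does not rule out a real elevation.

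Do not make significance under both equations a condition for a claim, and do not rely on a test of the change in gap as the cure. Step 5 of the working shows that the first can hide a real elevation of about 0.2 points, and that neither deals with ordinary lag. State separately that lag remains a limit of this check, since FGM on drug ends at month 3.

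The cost is wording in item 9 and in the detailed analysis plan before database lock. No new visits or measurements are needed. The downside is one more secondary comparison, and some results will have to be reported as inconclusive.
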